#### Aim 1.

To test for differences in improvement between the three groups on the primary outcomes for mood (HDRS), everyday function (SDS), and executive function (TMT-4), we will use multilevel modeling [93–95]. Multilevel modeling is a powerful and flexible statistical procedure that estimates intercepts and slopes for each individual (level 1) as well as intercepts and slopes for the average individual (level 2) over time using Maximum Likelihood (ML) estimation [93–96]. All analyses will adjust for gender and race/ethnicity (centered at their respective means). Time will also be centered so that the intercept reflects scores at week 4 (middle of the trial). To test whether average scores at week 4 and rate of change differs among the groups (PS/EF CCT, verbal CCT, and waitlist control), dummy variable coding will be used with 1 indicating membership and 0 indicating non-membership. With each covariate centered at its mean, the intercept will correspond to the mean of the reference group at week 4 (waitlist control) and the slope will reflect the difference between the groups included in the model (PS/EF CCT, verbal CCT) and the reference group (dummy coded variable excluded from the model). Because time can be centered at any point in the trial, we will also be able to run models with time centered at weeks 0 and 8 so that the intercept reflects scores at these points in the trial. This will allow us to test the hypothesis that PS/EF-focused CCT is more efficient, and therefore leads to faster improvement, than verbal-focused CCT or waitlist control. The −2LL (−2 Log Likelihood) test will be used to test model fit [94,95].

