### Statistical Analysis and Sample Size

Prior to conducting any tests of hypotheses, all data will be reviewed for extreme values using boxplots, scatterplots, histograms, and normal probability plots. When distributional assumptions are not met, data will be transformed or nonparametric procedures will be used. Descriptive statistics will be used to characterize the sample with regard to demographic and clinical characteristics including but not limited to age, education, race/ethnicity, gender, and depression severity.

In this study, missing data patterns will be analyzed explicitly. Data will not be assumed to be missing completely at random (MCAR) or missing at random (MAR). Rather, this assumption will be explicitly tested predicting “missingness” (missing = 1 and not missing = 0) at all assessment points post-baseline with baseline predictors (e.g., clinical, demographic, neuropsychological, and MRI), which can be accomplished in a logistic regression framework. More advanced approaches to handling missing data such as multiple imputation [91] or maximum likelihood estimation will be used rather than older, more biased approaches such as mean substitution, listwise or casewise deletion, or linear regression [92].

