#### Power.

Our preliminary study, with a sample of 46 participants, found significant within-subjects improvement across all outcomes and significant between-group differences in measures of EF and PS, with medium to large effect sizes for all findings [60]. Thus, with a recruitment goal of 90 participants in the current study, we expect to have significantly more power than our previous study. The power analyses for the current study were conducted using the pwr [98] and longpower [99,100] packages in R [101]. To power the proposed study at the 0.8 level (3 group RCT) to detect a medium between-group effect size (α = 0.05, two-tailed) with 20% attrition (a reasonable estimate based on our previous study [60] and consistent with dropout rates in psychotherapy RCTs [102]) would require a total sample of 195 or 65 per group. While this is obviously not feasible in a 3-year study (2.5 years actual recruitment, including database preparation, cleaning, and publication time at the end of the study) supported by a small grant mechanism, our proposed sample is twice that of our prior study. Also, in a previous study looking at CCN activation using the emotional go/no go task, significant activation was found in a number of different areas of the CCN with only 24 participants [103]. With a proposed sample size of 90, we are confident about detecting medium to large effect sizes across our proposed cognitive and neural activation variables of interest.

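### Maximum likelihood for the Aim 1 model makes standard errors about 2% (rate of change) to 3–5% (level) too small at 90 participants; report the contrasts from REML instead

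*Protocol article*

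**What the plan says.** Under Aim 1, the protocol article analyses HDRS, SDS and TMT-4 with multilevel models that estimate individual and average intercepts and slopes "over time using Maximum Likelihood (ML) estimation". The model has two arm dummies against waitlist, tests both the level at week 4 and the rate of change, and adjusts for gender and race/ethnicity. It can be re-centred so that the level refers to week 0 or week 8. The same section says that the −2LL "test will be used to test model fit".

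On missing data, Statistical Analysis and Sample Size says that "multiple imputation [91] or maximum likelihood estimation will be used rather than older, more biased approaches", so participants with incomplete follow-up are meant to stay in the model.

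The Power section works "with a recruitment goal of 90 participants in the current study". It says that a study powered "to detect a medium between-group effect size (α = 0.05, two-tailed) with 20% attrition" "would require a total sample of 195 or 65 per group". The article mentions neither REML nor a degrees-of-freedom method, and it does not say whether group contrasts are referred to a z or a t distribution.

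**The concern.** ML estimates variance components as if the fixed effects were known, so it divides by too large a number. With hundreds of people per arm this does not matter. With about 30 per arm, several arm and time terms, and a covariate with an unstated number of categories, the components and the standard errors built on them are biased downward. The bias always goes the same way: intervals too narrow and p values too small. It touches every group contrast on the three primary outcomes and is larger for the level contrasts, which are themselves planned tests. At stake is a modest excess of false positives that a different software option would remove.

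**Working it through.** **The plan's own figure.** The article states no error rate for the ML model. Its one calculated figure is the required sample of 195. Taking a medium effect as Cohen f = 0.25 (an assumption, as no value is given), a one-way ANOVA with three groups, two-sided 0.05 and 80% power needs 52.4 per group. Then 52 / 0.8 = 65 per group and 3 × 65 = 195, which reproduces the figure.

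**Inputs.**
- N = 90, about 30 per arm (Power). Applying the 20% attrition gives 90 × 0.8 = 72 completers, a number that the article does not state.
- Between-person parameters p for a rate-of-change contrast: time plus two arm-by-time terms, p = 3.
- For a week-4 level contrast: intercept, two arm terms and the covariate terms. The number of race/ethnicity categories is not given, so 2 to 5 covariate terms are assumed, giving p = 5 to 8.

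**Formula.** For a between-person contrast in a balanced design, the ratio of ML to REML standard error is r = √((N − p)/N). The size of a nominal 5% test is 2·P(T with N − p df > c·r), where c is 1.96 for a z reference or the 97.5% t quantile for a t reference.

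| Contrast | N | p | r | ML, z | ML, t | REML, z |
|---|---|---|---|---|---|---|
| Rate of change | 90 | 3 | 0.983 | 5.7% | 5.4% | 5.3% |
| Level, 2 covariate terms | 90 | 5 | 0.972 | 6.0% | 5.7% | 5.3% |
| Level, 5 covariate terms | 90 | 8 | 0.955 | 6.5% | 6.1% | 5.3% |
| Rate of change | 72 | 3 | 0.979 | 5.9% | 5.5% | 5.4% |
| Level, 2 covariate terms | 72 | 5 | 0.965 | 6.3% | 5.8% | 5.4% |
| Level, 5 covariate terms | 72 | 8 | 0.943 | 6.9% | 6.4% | 5.4% |

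The REML column isolates the effect of using z instead of t. At N = 90 that alone gives about 5.3%; ML adds the rest.

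**Simulation under no treatment effect.** There were 4,000 trials per scenario (Monte Carlo standard error about 0.4 points), with 90 participants, six per arm dropping out and their observed visits kept. ML and REML were fitted to the same data. Assumed values: random-intercept SD 1.0, random-slope SD 0.35 per four weeks, correlation −0.2, residual SD 0.7. Three scenarios were run: visits at weeks 0, 4 and 8 with 2 or 5 covariate terms, and the same visits plus a fourth at week 20 with 5 terms.

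| | Rate of change | Level at week 4 |
|---|---|---|
| Mean SE ratio, ML to REML | about 0.98 | 0.95–0.97 |
| ML, z | 5.9–6.5% | 5.9–6.2% |
| ML, t (69 df) | 5.5–6.0% | 5.4–5.7% |
| REML, z | 5.4–6.0% | 4.8–5.2% |
| REML, t (69 df) | 5.1–5.4% | 4.5–4.9% |

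At the same z reference, moving from REML to ML adds about 0.5 points for slopes and 0.8–1.4 points for levels. The ML likelihood-ratio test of the two slope differences, which needs no choice between z and t, rejects in 5.6–5.8% of trials.

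Both checks are for the level at week 4. The level at week 0 or 8 combines the week-4 level and slope terms, so its shortfall should be of the same order; it was not simulated separately.

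**The case against.** ML is a standard estimator for growth models. The words come from a general description of multilevel modelling, and ML is required if the −2LL comparisons involve models with different fixed effects. All of that stands: naming ML is not a mistake. It does not follow that the reported estimates, intervals and p values must come from the ML fit, because the two uses can be separated.

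It is also fair to say that the z or t reference and the degrees-of-freedom method are details that an article may leave to an analysis plan. Their absence is therefore not criticised here. The ML bias does not depend on them: it remains with a t reference and in the likelihood-ratio test.

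A reader might infer that the tests run at 6–7%. The documents do not support that:
- The 6.9% value needs exactly 72 participants, five covariate terms, a z reference and the level contrast, all together.
- A completers-only model is not planned. Participants with partial data stay in, and Criteria for Early Discontinuation keeps non-adherent participants in the intent-to-treat analyses.
- Gender and race/ethnicity main effects use up no parameters for the slope contrasts.

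Nor should the whole gap between ML with z and REML with t be put down to ML, since that comparison changes two things at once. The testing of three primary outcomes is a separate matter and adds nothing to this point.

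**Conclusion.** The point holds as a small, one-directional bias in a stated method. On the planned 90 participants, ML standard errors are about 2% too small for rate-of-change contrasts and about 3–5% too small for level contrasts. By formula, tests at a nominal 5% run at roughly 5.4–6.1% with a t reference and 5.7–6.5% with a z reference; the simulation agrees within its Monte Carlo error. About 6% is a fair one-number summary. The result rests on assumed variance components, on 2 to 5 covariate terms, and on partial data being kept as the article describes. This is a worthwhile refinement of small consequence, not a flaw that threatens the trial's conclusions.

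**What to change.** Add one sentence to Aim 1: fixed-effect estimates, confidence intervals and p values for the group contrasts come from a REML fit with Kenward-Roger or Satterthwaite degrees of freedom, and ML is used only for −2LL comparisons of nested models that differ in fixed effects. REML is likelihood-based and uses all available visits, so the approach to missing data is unchanged.

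The cost is a software option and slightly wider intervals. From the change of estimator alone, standard errors grow by about 2% for rate of change (1/0.983 = 1.017) and 3–5% for levels (1/0.972 = 1.029 to 1/0.955 = 1.047).

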#### Aim 2.

To determine whether PS/EF-focused CCT leads to greater CCN activation on the emotional go/no go task (primary fMRI outcome), we will conduct independent-sample t-test on the contrast images (i.e., correct no-go events minus correct go events for different emotional combinations and for the collapsed faced over face valence). The group differences in connectivity from the dynamic causal modeling (DCM) and from the resting-state CCN connectivity analyses will be examined. In addition, the correlation analysis between the pre and post-treatment brain activation and connectivity changes and the symptom improvement will be examined. To determine whether PS/EF-focused CCT leads to increased activation and connectivity in the CCN compared to verbal-focused CCT or waitlist control, we will use a regressed change model [96] on CCN connectivity index scores (secondary fMRI outcome). Analyzing two time-points using simple change scores can be problematic because subtracting the pre-score (Y1) from post-score (Y2) does not take unreliability into account. Reliability of change scores tends to be low and decreases as the correlation between the pre-test and post-test increase. Unreliability, therefore, tends to increase change scores from t1 to t2. Consequently, simple change scores tend to overcorrect the post-score (Y2) by the pre-score (Y1). This problem can be averted by adopting a regressed change procedure [96,97], which simply treats the pre-score (Y1) as a covariate effectively removing all correlation of the post-score (Y2) from the pre-score (Y1). In this particular instance, CCN connectivity index scores for each subject at t2 (week 8) will be included in the model as Y2 (outcome) and their CCN connectivity index scores at t1 (week 0) will be included in the model as the Y1 covariate. Treatment condition will also be dummy-coded in this model so that the intercept corresponds to the mean of the reference group (waitlist control) and the slope will reflect the difference between the groups included in the model (PS/EF CCT, verbal CCT) and the reference group, which is excluded from the model.

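### The Aim 1 growth model never conditions on the baseline score, giving up precision that the trial needs and could have at almost no cost

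*Protocol article*

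**What the plan says.** The Aim 1 section names HDRS, SDS and TMT-4 as primary outcomes. It fits a multilevel model by maximum likelihood (ML), with an intercept and slope for each participant and dummy variables for arm. The stated purpose is "To test whether average scores at week 4 and rate of change differs among the groups". Time is centred at week 4, described as the middle of the trial, and further models are centred at weeks 0 and 8. On covariates the section says: "All analyses will adjust for gender and race/ethnicity (centered at their respective means". The participant's own week-0 score is not listed as a covariate, and nothing holds the arms' week-0 means equal.

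The Aim 2 section takes a different line for the connectivity index, its secondary fMRI outcome. It says "Analyzing two time-points using simple change scores can be problematic" and enters the pre-score as a covariate.

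The Randomization section places baseline neuropsychological testing and the baseline scan before assignment. The Power section says that 80% power for a medium effect with 20% attrition "would require a total sample of 195 or 65 per group", and that 90 will be recruited.

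**The concern.** Week 0 is measured before randomisation, so any baseline difference between arms is due to chance. A model that lets the arms differ freely at week 0 does not use this. The variance of its slope contrast then carries the full noise of the baseline measurement, and a chance imbalance at week 0 passes into the estimated rate of change through regression to the mean.

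The protocol states the case for using the pre-score as a covariate, but applies it to one secondary imaging measure and not to the three primary clinical and cognitive outcomes. Since the trial is, by its own account, less than half the size it needs, unused precision in the primary comparisons matters.

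**Working it through.** **The plan's sample size.** Inputs from the Power section: two-sided α = 0.05, power 0.80, three groups, 20% attrition. The medium effect has no number; I take Cohen's f = 0.25. A one-way ANOVA (noncentral F) then needs 52.4 per group. 52/0.8 = 65 per group, and 3 × 65 = 195, so the stated figure is reproduced. With 90 recruited and equal allocation there are 30 per arm, or 30 × 0.8 = 24 after 20% attrition.

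**What the slope contrast is.** For visits at 0, 4 and 8, the centred times are −4, 0 and +4, with sum of squares 32. The slope weights are −4/32, 0 and +4/32, that is −0.125, 0 and +0.125. Week 4 has no weight, and the slope is (week 8 − week 0)/8. A direct ML fit with random intercepts and slopes on simulated complete data, with gender as a main effect, confirmed this: the arm-by-time coefficients were −0.07502 and −0.19974, identical to the arm differences in (week 8 − week 0)/8.

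**The level contrasts.** With the same balanced data, the intercept at week 4 is the plain mean of the three visits (1/3 each). At week 8 the weights are 1/3 − 1/2 = −1/6, then 1/3, then 1/3 + 1/2 = 5/6. Both include week 0, but neither conditions on it.

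**Precision, equal variances assumed.** Let ρ be the correlation between weeks 0 and 8 and s the common SD.
- Variance of change: 2(1 − ρ)s².
- Variance after adjusting for baseline: (1 − ρ²)s².
- Fraction removed: 1 − (1 + ρ)/2 = (1 − ρ)/2.

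The protocol gives no ρ, so a range is shown:

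| ρ | 0.3 | 0.5 | 0.7 | 0.8 | 0.9 |
|---|---|---|---|---|---|
| Removed | 35% | 25% | 15% | 10% | 5% |

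**Precision, unequal variances.** Let k be the week-0 SD divided by the week-8 SD. The variance ratio, adjusted to change, is (1 − ρ²)/(k² + 1 − 2ρk), so the fraction removed is (k − ρ)²/(k² + 1 − 2ρk), which is never negative. SDs by visit are not given, so k is also an assumption:

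| k | ρ = 0.3 | ρ = 0.5 | ρ = 0.7 |
|---|---|---|---|
| 1.0 | 35% | 25% | 15% |
| 0.8 | 22% | 11% | 2% |
| 0.7 | 15% | 5% | 0% |

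**Power, for illustration.** Take one pairwise comparison with an assumed difference of 0.5 week-8 SD, 24 per arm, equal variances and a normal approximation. Change score against baseline-adjusted: 31% v 44% at ρ = 0.3, 41% v 52% at 0.5, and 61% v 68% at 0.7.

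**Attrition.** Assume 20% lost by week 8, half of them before week 4, and a random-intercept covariance. Relative to leaving the arms' week-0 means free, constraining them equal multiplies the ML slope variance by 0.64, 0.75 and 0.86 at ρ = 0.3, 0.5 and 0.7. With complete data the factors are 0.60, 0.73 and 0.84. Most of the gain survives dropout.

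**The case against.** A growth model with random intercepts and slopes is a standard analysis and speaks directly to the hypothesis of faster improvement. Several stronger readings are tempting, and the protocol does not support them.

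- *That the slope test simply is the change score.* This is exact only with complete data at the three acute visits. ML keeps partial data and then uses week 4. In a simulated fit with 20% of week-8 values missing, the ML contrasts were −0.066 and −0.217, against −0.137 and −0.228 for completers' change. The section also does not say whether the 3-month visit enters the slope. If it did, at about week 20, the weights (times 8) would be −0.29, −0.14, 0 and +0.43.
- *That Aim 2 rejects the Aim 1 analysis.* Its objection is worded for two time-points and concerns unreliability, and Aim 2 itself still correlates pre-post changes with symptom improvement. The mismatch is one of principle, not a direct contradiction.
- *That 15–35% of the variance is wasted.* That range needs both ρ between 0.3 and 0.7 and equal variances. HDRS is an entry criterion (a score of at least 12 or a diagnosis, and below 30), which might narrow its week-0 spread. SDS and TMT-4 are not entry criteria.
- *That gender and race/ethnicity cannot affect the slope.* This holds for main effects with complete data, but the text does not say that they enter only as main effects.
- *That the contrast is biased.* Baseline testing precedes randomisation, so it is not.

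What remains after these limits is that none of the planned contrasts conditions on the baseline score.

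**Conclusion.** The point holds as a loss of efficiency, not of validity. The model as described leaves the primary comparisons unadjusted for a baseline score collected before assignment. The complete-data algebra is certain. The size is not, because it depends on a correlation and an SD ratio that the protocol does not report. Across the assumed values shown above, the saving runs from nothing to about a third of the change-score variance. Adjustment cannot raise the large-sample variance. It would not close the gap between 90 and 195 participants, but a trial that far short of its own requirement has good reason to take the gain.

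**What to change.** For HDRS, SDS and TMT-4, state one of two analyses:

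1. Keep week 0 as an outcome in the repeated-measures model and constrain the arms' week-0 means to be equal, which assignment after baseline testing justifies.
2. Model weeks 4 and 8 with the week-0 score as a covariate, and test arm-by-visit contrasts.

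Gender and race/ethnicity may stay in either. The text should also say whether the 3-month visit enters the model. The cost is a sentence or two in the analysis section; Table 4 already schedules all three measures at week 0.

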#### Aim 2.

To determine whether PS/EF-focused CCT leads to greater CCN activation on the emotional go/no go task (primary fMRI outcome), we will conduct independent-sample t-test on the contrast images (i.e., correct no-go events minus correct go events for different emotional combinations and for the collapsed faced over face valence). The group differences in connectivity from the dynamic causal modeling (DCM) and from the resting-state CCN connectivity analyses will be examined. In addition, the correlation analysis between the pre and post-treatment brain activation and connectivity changes and the symptom improvement will be examined. To determine whether PS/EF-focused CCT leads to increased activation and connectivity in the CCN compared to verbal-focused CCT or waitlist control, we will use a regressed change model [96] on CCN connectivity index scores (secondary fMRI outcome). Analyzing two time-points using simple change scores can be problematic because subtracting the pre-score (Y1) from post-score (Y2) does not take unreliability into account. Reliability of change scores tends to be low and decreases as the correlation between the pre-test and post-test increase. Unreliability, therefore, tends to increase change scores from t1 to t2. Consequently, simple change scores tend to overcorrect the post-score (Y2) by the pre-score (Y1). This problem can be averted by adopting a regressed change procedure [96,97], which simply treats the pre-score (Y1) as a covariate effectively removing all correlation of the post-score (Y2) from the pre-score (Y1). In this particular instance, CCN connectivity index scores for each subject at t2 (week 8) will be included in the model as Y2 (outcome) and their CCN connectivity index scores at t1 (week 0) will be included in the model as the Y1 covariate. Treatment condition will also be dummy-coded in this model so that the intercept corresponds to the mean of the reference group (waitlist control) and the slope will reflect the difference between the groups included in the model (PS/EF CCT, verbal CCT) and the reference group, which is excluded from the model.

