## METHODS

### Study Design Features and Rationale

Ninety young adults exhibiting mild to moderate depressive symptoms will be randomized in an 8-week computerized cognitive training (CCT) trial delivered via smartphone application. Mobile-based CCT was chosen as it is particularly relevant for young adults, with 92% of those aged 1829 owning a smartphone [81]. Mobile CCT is also consistent with the goal of personalizing medicine as it is easily accessible, inexpensive, noninvasive, and scaled to the skill level of each individual. Neuropsychological and clinical assessments will take place at Queens College, City University of New York, and fMRI will be conducted at The Graduate Center’s MRI facility, the Advanced Science Research Center. Participants will be randomized to one of three conditions: processing speed/executive functioning (PS/EF) CCT, verbal ability CCT (active control), or waitlist control (undergo assessment and imaging procedures and will be not be given access to the training program until 8-week completion). The randomization sequences will be balanced in blocks of random size to prevent researchers from guessing what the next participant’s condition assignment might be. In order to reduce expectancy bias, the informed consent signed by all participants prior to participation will not indicate which condition is the intervention, the active control, or the waitlist control. Instead, the consent will indicate that the participant will be assigned to one of three groups, two which target different aspects of brain functioning and the third which will begin cognitive training after 8 weeks.

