### Study Measures

Study measures with time-points of administration are listed in Table 4 At screening, the ADIS-IV, HDRS, BDI-II, SDS, and WTAR will be administered, and current medications will be documented. The HDRS, BDI-II, and SDS will be administered again at weeks 0, 4, and 8, and 3-month follow-up. At weeks 0, 4, and 8, and 3-month follow-up, the neuropsychological battery will be administered, and current medications will be documented. At weeks 0 and 8, participants will undergo an MRI scan of the brain. The MRI scan will include the following sequences: T1 Magnetization-Prepared Rapid Gradient-Echo (MP-RAGE), as well as a task-based fMRI sequence consisting of the emotional go/no-go task, and pre-post task-based resting-state fMRI scans (see Table 5).

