### Hypotheses

The primary aim of the study is to determine whether PS/EF-focused CCT is superior to, and leads to faster improvement than, verbal ability-focused CCT and waitlist control. Hypothesis 1: there will be greater improvement in mood, cognition, and everyday functioning in participants randomized to CCT (both PS/EF and verbal) compared to waitlist control. Hypothesis 2: there will be greater improvement in EF and PS outcomes in participants randomized to PS/EF CCT compared to verbal CCT and waitlist control. Hypothesis 3: there will be faster improvement in mood, cognition, and everyday functioning in participants randomized to PS/EF CCT compared to verbal CCT and waitlist control.

The secondary aim of the study is to determine whether PS/EF-focused CCT leads to greater change in CCN activation (task-based fMRI) and connectivity (resting state fMRI) than verbal ability-focused CCT and waitlist control. Hypothesis 1: there will be a greater increase in CCN activation and connectivity among participants randomized to PS/EF CCT and verbal CCT compared to waitlist control. Hypothesis 2: there will be a greater increase in CCN activation and connectivity among participants randomized to PS/EF CCT compared to verbal CCT. Hypothesis 3: clinical improvements will be positively associated with an increase in CCN activity and connectivity.

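### The primary fMRI outcome is given a two-group t-test with no stated arms, visit or week-0 term, while the baseline-adjusted three-arm model is specified only for the secondary connectivity index

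*Protocol article*

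**What the plan says.** The design has three arms: "Participants will be randomized to one of three conditions" (Study Design Features and Rationale). Scans are paired: "At weeks 0 and 8, participants will undergo an MRI scan of the brain" (Study Measures).

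The Hypotheses section states the imaging aim as "greater change in CCN activation (task-based fMRI) and connectivity (resting state fMRI) than verbal ability-focused CCT and waitlist control". Under it, Hypothesis 1 sets both training arms against waitlist. Hypothesis 2 is that "there will be a greater increase in CCN activation and connectivity among participants randomized to PS/EF CCT compared to verbal CCT".

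The Aim 2 analysis text treats the two imaging outcomes differently.

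- **Primary.** The outcome is "greater CCN activation on the emotional go/no go task (primary fMRI outcome"), and the method is "we will conduct independent-sample t-test on the contrast images". The images are described as "correct no-go events minus correct go events for different emotional combinations", and also collapsed over face valence.
- **Secondary.** Here "we will use a regressed change model [96] on CCN connectivity index scores (secondary fMRI outcome"). The text then sets out this model in full: the week-8 score is the outcome, the week-0 score is the covariate, and treatment is dummy-coded with waitlist as reference.

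Between the two, the paragraph explains why simple pre-post change scores can be problematic and says that regressed change avoids the problem. Change in activation also appears in a planned correlation with symptom improvement, but that is not a comparison between arms.

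**The concern.** An independent-sample t-test compares two groups on one value, or one image, per person. The imaging aim needs a comparison of change among three groups. The contrast images as described are differences between task conditions inside a scan, so nothing in the stated test refers to the week-0 scan. Nothing in it says which groups are compared either.

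The model that would fit the aim is written out a few sentences later, with its justification, and is then applied only to the secondary outcome. The primary imaging outcome therefore gets the weaker analysis.

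The Depressive symptoms criteria section calls showing the mechanism of action the study's central aim, although the Hypotheses section ranks the imaging comparison as secondary. The Power section says that 195 participants would be needed for a medium effect, against 90 planned. A trial that acknowledges this shortfall has good reason to use the precision its baseline scans already offer. Leaving the visit and the pairs open also allows them to be chosen after the data are seen.

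**Working it through.** **1. The plan's own figure.** The Power section gives 195 in total (65 per group) for three groups, a medium effect, two-tailed alpha 0.05, power 0.80 and 20% attrition.

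- Three-group one-way ANOVA, with medium taken as f = 0.25: 52.4 per group, 157.2 in total; 157.2 / 0.8 = 196.5. This is within 3% of 195, and 52 / 0.8 = 65 exactly.
- Two-sample t-test, with medium taken as d = 0.5: 64 per group; 64 / 0.8 = 80; 3 × 80 = 240. This does not reproduce 195.

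The stated sample size therefore matches a three-group analysis, not the two-group test named for the primary fMRI outcome.

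**2. The two readings of the t-test.**

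- Week-8 images only: the test compares levels at week 8. It does not use baseline, and chance differences between arms at week 0 enter the estimate.
- Week-8 minus week-0 images: the test addresses change, but through the simple change score that the paragraph calls problematic.

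**3. Relative precision.** Assume equal variance (set to 1) at both visits and a common week 0 to week 8 correlation ρ. The article gives no ρ, so 0.3 to 0.7 is an assumed range. The variance per person behind the treatment contrast is:

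- week 8 only: 1
- difference: 2(1 − ρ)
- baseline-adjusted: 1 − ρ², ignoring the one degree of freedom spent on the covariate

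The ratio of adjusted to difference is (1 − ρ²) / [2(1 − ρ)] = (1 + ρ)/2.

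| ρ | Difference | Adjusted | Adjusted / week 8 only | Adjusted / difference |
|---|---|---|---|---|
| 0.3 | 1.40 | 0.91 | 0.91 | 0.65 |
| 0.5 | 1.00 | 0.75 | 0.75 | 0.75 |
| 0.7 | 0.60 | 0.51 | 0.51 | 0.85 |

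With 90 / 3 = 30 per arm and 20% attrition, about 30 × 0.8 = 24 per arm remain (equal arms assumed). At ρ = 0.5 adjustment makes 24 per arm worth 24 / 0.75 = 32.

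**4. Illustrative power for one pairwise comparison.** Assume d = 0.5 in week-8 SD units. Power ≈ Φ(d√(n/2)/σ − 1.96), with σ² taken from the table. For n = 24 and week-8 images only: 0.5 × √12 = 1.73, and Φ(1.73 − 1.96) = 41%.

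| n per arm | ρ | Week 8 only | Difference | Adjusted |
|---|---|---|---|---|
| 24 | 0.3 | 41% | 31% | 44% |
| 24 | 0.5 | 41% | 41% | 52% |
| 24 | 0.7 | 41% | 61% | 68% |
| 30 | 0.3 | 49% | 37% | 53% |
| 30 | 0.5 | 49% | 49% | 61% |
| 30 | 0.7 | 49% | 71% | 77% |

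**5. Repeated t-tests.** If the t-test were run for all three pairs at 0.05 each, the familywise error would be about 1 − 0.95³ = 14%. This treats the pairs as independent and is only approximate, because pairs share arms.

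**The case against.** A reader might infer that the plan discards the baseline scan. The text does not support that. No visit is named, so difference images are possible, and the planned correlation with symptom improvement does use pre-post activation change.

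A reader might also infer that one arm has to be left out. That does not follow either. The two group-comparison hypotheses for imaging can each be tested with a two-sample test: pooled training against waitlist, which uses all three arms, and PS/EF against verbal.

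Nor is bias shown. Allocation is randomised, so week-8, difference and baseline-adjusted comparisons all target the group effect without bias. Chance imbalance at week 0 passes directly into the result only if week-8 images alone are used.

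The sentence introducing the regressed-change model mentions activation as well as connectivity, so the authors may have meant it for both. Visit and pairs are also details that a journal article can leave to an analysis plan that is not shown here. Finally, the gain depends on ρ: at 0.3 the variance falls only 9% against week-8 images.

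All of this limits the point, but a core remains. The article does not merely leave the analysis unstated: it fixes a named test for the primary outcome, and in the same paragraph fixes and justifies a better-fitting model that it specifies for connectivity scores only. Under either reading of the visit, the t-test is the less precise choice.

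**Conclusion.** The point holds as a mismatch between the stated test and the stated aim, with a loss of precision. The t-test for the primary fMRI outcome carries no arms, visit or week-0 term, whereas the aim is comparative change in three arms and the secondary outcome gets a model that matches it.

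Adjustment would cut variance by 9% to 49% against week-8 images and by 15% to 35% against difference images. These ranges rest on the assumed ρ of 0.3 to 0.7 and on equal variances at the two visits. The power figures rest in addition on an assumed d of 0.5 and equal arms, and are illustrative only.

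The documents do not show a biased estimate, a lost arm or a discarded scan. The point should be fixed; it does not make the imaging comparison invalid.

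**What to change.** Extend the regressed-change model already written for connectivity to the primary fMRI outcome:

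- outcome: the week-8 no-go minus go contrast
- covariate: the same contrast at week 0
- arm: a three-level factor
- contrasts from that one model: PS/EF versus verbal, PS/EF versus waitlist, and pooled training versus waitlist

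Fit it to a CCN region-of-interest summary, which would need to be defined, or voxelwise with the week-0 covariate specific to each voxel. How to rank the separate emotion contrasts is a different decision and need not be settled here.

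Both scans are already scheduled, so no new data are needed. The cost is revised wording and a small amount of extra analysis work. The Results section places analysis after recruitment ends, so the change can be made before outcome data are examined.
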